### *Intervention*

Upon completion of the baseline measures, participants allocated to the intervention condition will be invited (via Qualtrics and an email “triggered” when measures are completed on Qualtrics) to attend a drop-in session at the sling surgery, on a Thursday, Friday or Saturday, while their infant is between 0 and 6 weeks of age. Participants will be asked to book on to a session in order to monitor demand for free slings from the Sling Surgery and ensure that slings that have been put aside for use by the study are available on the day that the participant attends.

A window of 6 weeks has been given, as recommended by the sling surgery, as the researchers recognise that each birthing experience is different and mothers may vary in the time it takes for them to feel able to undertake a trip to the sling library following giving birth.

The drop-in sessions that participants will be invited to attend are those run regularly by the Sling Surgery, and are open to the public. Typically parents are able to attend these sessions at any point during the two-hour period that they run and are welcome to stay for as long as they like within this time period. Parents attend these sessions seeking advice for slings that they are currently using, or the opportunity to try using a sling for the first time before buying

or hiring.

Participants will be instructed to identify themselves as a participant in the study when they attend their initial session, and whenever they otherwise interact with the Sling Surgery. This is so that their data is stored correctly and so that they are not accidentally charged for any of the Sling Surgery services.

Furthermore, the research team has created a checklist (based on the standard drop-in session procedure already in place) to be used during sessions with study participants. This is in order to support standardisation of session content across each participants' sessions, and also to make the study more replicable. This checklist may be found in Appendix T. By identifying themselves as study participants, participants will ensure they are given a session using this checklist.

Typically a parent or parents will sign-in, giving their name, email address, postcode, how they have travelled to the session, their child's name and age, and whether they require support that day). They will then be greeted by either a sling consultants or a voluntary peer supporter. On busy days there may be a short wait before someone is available to greet and work with the parent. At this point participants will state that they are a participant in this study. Following the session checklist, participants will be offered sling training and advice, and a sling use demonstration. Participants will learn how to safely use one of three different types of sling (either a stretchy, a close caboo, or one type of buckle carrier, dependent on the parent and infant's needs and preference) with a weighted demonstration doll before practicing with their own baby. Participants will be given this sling to hire for free for the duration of the study and a reminder leaflet containing sling safety information (Appendix U).

In these drop-in sessions, rather than being private 1:1 consultations, all contact between parents and Sling Surgery staff takes place within the same room. Thus while each parent, or set of parents, is met individually, if a number of parents have the same question, or a number are participants in this study, a Sling Surgery staff member may end up training, advising and demonstrating to a group of parents, rather than providing 1:1 support. Because everything takes place within the one room (aside from completion of the paperwork for hiring or buying a sling), this offers parents the opportunity to meet and support each other, and in particular discuss their experiences of sling use so far.

Following this session, participants will be sent an email which contains a link to a webpage with reminder information about their hire sling and how to use it, as well as an invitation to join the online sling community for further support, and information about the other support available through the sling surgery (Appendix U). Staff at the Sling Surgery will create a new “library” on their myTurn database in order to send these emails which are tailored to this study (e.g. which do not mention hire fees etc.).

Throughout the study, participants will be able to access the sling surgery’s support services as regularly as they like, including those that do not focus specifically on sling use. Participants will also be able to swap their sling if they suspect that another sling may be more suited to themselves and their infant. This is in line with the sling surgery’s current standard practice.

### *Control Participants*

Control participants will be asked to complete the same measures as participants in the intervention condition, at the same time points, again via email or text depending on their stated preferred method of communication. However control participants will not be offered the intervention (sling hire, training and support) when their infant is between 0 and 6 weeks old, but instead will be offered one month's free sling hire, training and support, following completion of the study. Via email, which will be triggered when participants complete their final set of measures on Qualtrics, participants will be asked to book on to a session in order to monitor demand for free slings from the Sling Surgery and ensure that slings that have been put aside for use by the study are available on the day that the participant attends.

### *Data Collection*

When their infant is 0 to 6 weeks old participants will complete baseline measures. For intervention participants completion of baseline measures will be prior to attending the sling surgery session. Currently these are due to include measures of PND (EPDS, DASS21), attachment (ECR-S), a measure of sling and buggy use and also of use of sling surgery services, a breastfeeding measure, and measures of wellbeing (WEMWBS/SWEMWBS), parenting (PSCS, CEQ), infant temperament (IBQ-R VSF) perceived social support (SPS) and general demographics (as mentioned in the *participants* section above).

As part of this feasibility study, it would be helpful to examine how long is needed before an effect of sling use upon maternal mental health, wellbeing and parenting may be seen. This information could support future RCTs in deciding the duration of a sling use intervention condition. It was agreed that an additional time-point, midway through the study, may help to narrow down the point at which an effect of sling use may be seen. Thus, 6 weeks

after completion of baseline measures, both intervention and control participants will be asked (via text or email - see below) to complete Time-2 (T2) measures online. These T2 measures are not the full battery of measures. Rather, participants in both groups will be asked about current sling use and use of sling surgery services (including whether they have swapped their sling). The EPDS will also be administered a second time at this time-point.

A further 6 weeks later (T3) participants in both conditions will be asked (via text or email - see below) to complete for a second time the full battery of measures that had been given at baseline (T1) (excluding demographic measures).

A text or email reminder (depending on each participant's stated preferred method of contact) will be sent each time that the participant is due to complete their next battery of measures. This message will contain a link to these measures (via Qualtrics).

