### *Ethical Implications*

Ethical approval will be sought from the University of Sheffield. As mentioned in the *Procedure* section above, during recruitment, participants will be given information explaining the aims and procedure of the study (please see Appendix Q). They will be asked to complete a consent form prior to participating in the study (Appendix R). It will be made clear that participants are free to withdraw their data at any time. Participants will also be debriefed at the end of the study (Appendix V).

As mentioned in the *Primary Measures* section above, during the study, it may be that participants score above the clinical threshold applied in NHS settings on the EPDS. Should this happen, participants will be sent a letter (please see Appendix E) recommending that they speak to their midwife or health visitor, and also their GP. The letter will be marked “Private and Confidential”.

It must be acknowledged that there is an incentive for participation in this study, in that participants in both conditions will receive sling hire and training for free, that they might have otherwise paid for. Furthermore, while control participants will receive the intervention (sling hire, training and support) following completion of the study, they will receive one month of free sling hire, support and training, the intervention participants will have received three months of free sling hire, support and training over the course of the study. While this discrepancy may appear unfair, it is commensurate with sling library advice and based on the different level of support needed in relation to infant age. Parents of very young infants usually require more support with sling use than parents of older infants.

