**You are now invited to attend a session at the Sheffield Sling Surgery.**

Please attend a session as soon as is convenient for you (if possible, within the next two weeks).

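### T2 and T3 are timed from the baseline questionnaire but the sling is received later, so attenders can have 0 to 6 weeks of sling access at T2, which weakens the question of how long an effect takes

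*Protocol*

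**What the plan says.** **Clock.** Under Data Collection, baseline has a six-week window: "When their infant is 0 to 6 weeks old participants will complete baseline measures". T2 comes six weeks "after completion of baseline measures, both intervention and control participants will be asked" to respond, and T3 follows: "A further 6 weeks later (T3) participants in both conditions will be asked". Both arms share this clock. The Design section calls the three assessments pre-, mid- and post-intervention.

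**Sling.** Baseline comes first: "For intervention participants completion of baseline measures will be prior to attending the sling surgery session". The Intervention section then invites the woman to a drop-in session "while their infant is between 0 and 6 weeks of age", and explains the wide window by saying that women differ in when they feel able to travel. The messages in Appendix S.7 and S.8 add a softer target: "Please attend a session as soon as is convenient for you (if possible, within the next two weeks". The Debrief section has the sling returned after T3.

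**Purpose of T2.** Data Collection says it would be useful to learn how long is needed before an effect appears, so as to guide the length of the intervention in later trials. An extra time point "may help to narrow down the point at which an effect of sling use may be seen". The EPDS is the only outcome scale named for T2; the full battery returns at T3.

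**Hire length and records.** Ethical Implications states that "the intervention participants will have received three months of free sling hire, support and training over the course of the study". Data Security and Management says that hire information is stored, so that the Sling Surgery can track when slings go out.

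**The concern.** The exposure whose time course is of interest starts at the session, but the assessments are counted from the questionnaire. The gap between the two differs from woman to woman, and the protocol expects it to. T2 therefore does not mark a fixed amount of sling access. If the EPDS showed no difference at T2, the result alone could not separate too short a period of use from late receipt in part of the group. A later trial that took its intervention length from the labels of 6 and 12 weeks could be misled.

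The questionnaire does not resolve this. The item in Appendix B asks how often the sling was used over the past six weeks and asks no start date. Proposed Analysis raises the possibility of repeating the analysis without intervention women who did not use the sling regularly, and there late receipt could be mistaken for poor adherence.

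Two passages also fit badly with the timing rules: the two-week request in Appendix S.7 and S.8, and the three months of hire in Ethical Implications.

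**Working it through.** **1. The plan's own calendar.** Timetable/Plan of work gives T1 from late February to late July 2019, T2 from April to mid-September, and T3 from mid-May to late October. Taking 25 February and 28 July as stand-ins for the T1 limits:
- 25 February + 6 weeks = 8 April; + 12 weeks = 20 May.
- 28 July + 6 weeks = 8 September; + 12 weeks = 20 October.

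This agrees with the stated windows to within their rounding. It is the Data Collection wording, not the calendar, that settles the baseline anchor.

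**2. Access as a function of delay.** Let b be infant age at baseline and s infant age at the session, with 0 ≤ b ≤ s ≤ 6 weeks (Intervention; Data Collection). The delay is D = s − b. At the scheduled times, access at T2 is 6 − D and access at T3 is 12 − D.

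| Delay D (weeks) | Access at T2 | Access at T3 |
|---|---|---|
| 0 | 6 | 12 |
| 2 | 4 | 10 |
| 4 | 2 | 8 |
| 6 | 0 | 6 |

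The rules alone give 0 to 6 weeks at T2 and 6 to 12 at T3 for attenders. At the limits, one woman's T3 access (6 weeks) equals another's T2 access (6 weeks). If every woman attends within two weeks of baseline, D ≤ 2 and the ranges are 4 to 6 and 10 to 12. A woman who never attends has zero at both. Questionnaires completed late would lengthen access somewhat.

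**3. How often access is short.** The protocol gives no distribution for b or s, so these are assumptions that show a range.
- *b uniform on 0–6, s uniform over the time left.* E[D] = E[(6 − b)/2] = 1.5, so mean access is 4.5 weeks at T2 and 10.5 at T3. P(D > 2) = (4 − 2 ln 3)/6 = 0.30 have under 4 weeks at T2. P(D > 3) = (3 − 3 ln 2)/6 = 0.15 have under 3 weeks. P(D > 4) = (2 − 4 ln 1.5)/6 = 0.06 have under 2 weeks.
- *b uniform on 0–2, s uniform over the time left up to 6.* E[D] = 2.5, so mean access at T2 is 3.5 weeks. P(D > 2) = (2 − 2 ln 1.5)/2 = 0.59 have under 4 weeks. P(D > 4) = (2 − 4 ln 1.5)/2 = 0.19 have under 2 weeks.
- *D uniform on 0–2 (request met).* Mean access is 5.0 weeks at T2 and 11.0 at T3; nobody has under 4 weeks at T2.

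**4. Session window against the two-week request.** For a woman who completes baseline after infant week 4, two weeks runs past week 6. At b = 6 the Intervention window has closed, while the request runs to 6 + 2 = 8 weeks.

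**5. Stated hire against the rules.** Hire runs from the session to T3, so its scheduled length is 12 − D, which is 6 to 12 weeks. The full 12 weeks occurs only when D = 0. Three months is at best the upper limit, not what every intervention woman receives.

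**The case against.** A reader might infer that the timing aim cannot be met. The documents do not support that. The aim is worded cautiously: T2 may help, and no duration recommendation is promised. Zero weeks of access at T2 needs baseline at birth and the session at exactly six weeks. The messages ask for attendance within two weeks, and under that reading access at T2 is 4 to 6 weeks. Even under the first uniform model only about 6% have under two weeks, so it would be wrong to say that most women had barely received the sling. Hire dates are held, so access time can be recovered.

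A reader might also infer that the baseline clock is the error. It is not. Controls have no session date, and the protocol requires the same time points in both arms. The intention-to-treat comparison then has a clear meaning: the effect of being offered a sling, at 6 and 12 weeks after baseline. Retiming to receipt would leave controls without an anchor and could bias the comparison.

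Nor should the lack of an analysis by access time be counted as an omission. A statistical analysis plan, not available here, may contain one.

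Finally, women choose when to attend, according to how able they feel. Early and late attenders may differ in recovery and mood, and there are only 25 to 30 women per arm. A comparison by weeks of access is not randomised. This objection stands and limits the remedy to description.

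What survives is that the permitted delay is wide, the labels hide it, and two pairs of statements do not agree.

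**Conclusion.** The point holds in a limited form. By the protocol's own rules, attenders have 0 to 6 weeks of sling access at T2 and 6 to 12 at T3, or 4 to 6 and 10 to 12 if the two-week request is always met; non-attenders have none. These ranges need no distributional assumption, only that questionnaires are completed on schedule. The illustrative means (3.5 to 5.0 weeks at T2) and the shares with under four weeks (0% to about 60%) depend entirely on the assumed attendance patterns.

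The aim of finding how long sling use must last is weakened, not defeated. At T2 it can be pursued only for the EPDS; for wellbeing and parenting T2 gives no answer whatever the hire date, because those scales are not given then. The randomised comparison is sound as the effect of the offer. The inconsistencies over the session window and the length of hire are real and need reconciling; this review takes no position on which statement should prevail.

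**What to change.** 1. Keep the common baseline clock and the intention-to-treat comparison, and state what it estimates: the effect of being offered a sling, 6 and 12 weeks after baseline.
2. Extract each intervention woman's first-hire and return dates from the hire records. Link them to the questionnaire data in time: the debrief sheet says that the University destroys contact details after sending it, and that women may ask the Sling Surgery to do the same once the sling is returned.
3. Report the distribution of weeks of access at T2 and T3, with non-attenders included as zero.
4. Qualify any statement about the duration needed by those weeks. Label any analysis by weeks of access as descriptive, because time of attendance is self-selected.
5. In the Design section, describe T2 as six weeks after baseline, not mid-intervention.
6. Reconcile the session window in the Intervention section with the two-week request in Appendix S.7 and S.8. Reconcile the three months in Ethical Implications with the Intervention, Data Collection and Debrief sections.

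The cost is a small data-linkage task and some rewording. The drawback is a weaker time-to-effect statement than the labels of 6 and 12 weeks suggest.

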### *Debrief*

Participants in both conditions will be debriefed following completion of measures at time-point 3. This will be sent via an email which will be triggered by Qualtrics when this final set of questionnaires is completed by the participant. For intervention participants, the email will also remind them to now return their sling, while, for control participants, the email will ask them to book on to a session at the Sling Surgery so that they may receive their sling training and begin their free sling hire. Examples of these emails may be found in Appendix S. A copy of the debrief sheet may be found in Appendix V.

### *Data Security and Management*

Data will be stored using Qualtrics. Using this programme, the data is password protected and only accessible by the research team. Identifiable data will need to be kept, as participants will need to be reminded to complete T2 and T3 measures via phone or email (whichever is their preferred method) at the correct times, and data analysis relies on matching participants' data from each time point.

Contact details, as well as information about each participant's sling hire and any other access to Sling Surgery services will be securely stored on both Qualtrics and the sling surgery myTurn hire system, which is also password protected and only accessible by Sling Surgery staff. This will allow the sling surgery to follow their standard practice and keep track of where and when slings have been hired out.

Only secure university or Sling Surgery email addresses will be used to contact participants and the sim card used to contact participants will be kept in a locked location only accessible by research team members.

### *Proposed Analysis*

As a feasibility study it is difficult to predict participant drop-out rate, and the impact that this may have on the results of the study. In order to control for drop-out, intention-to-treat (ITT) analysis will be used.

A mixed ANCOVA will be used to evaluate the relationship between sling provision and maternal mental health, wellbeing and parenting. This will include a comparison of both within-group pre- and post-intervention scores, and a between-group comparison of intervention vs. control group scores.

Attachment will be included as two covariates, as the measure of attachment used in this study produces two scores (*Avoidance* and *Anxiety*).

Thematic analysis will be used to evaluate the data collected from the two qualitative questions included at T3.

As a feasibility study, the impact of treatment fidelity on the results of the study is of interest. In order to examine this impact, it may be helpful to run the analysis again, this time excluding data from control participants who have used a sling, or accessed the sling surgery services over the course of the study. Similarly, it may be helpful to then re-run the analysis again, but this time excluding participants in the intervention condition who did not use their sling regularly. Through a similar process, it may be important to re-analyse the results of the study, investigating whether the frequency of participants' partners' sling use impacts upon these results.

It will be important to investigate whether the results of various demographic groups differ, in order to inform the inclusion or exclusion criteria of future RCTs. Frequencies and descriptive statistics derived from the demographic measures will be examined and presented. If possible, tests of difference will be conducted using this data, though this will of course depend upon the size of the demographic groups.

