## Aims and Hypotheses

A feasibility study is underpowered to reliably assess treatment effectiveness (Williams, 2016). Therefore the primary focus of a feasibility study is not hypothesis testing, though statistical analysis of between-group outcome differences may be conducted in a preliminary way in order to inform the sample size calculations of future RCTs (Williams, 2016). Instead, as a feasibility study, the focus of this study is on collecting information that will support the design of future studies, e.g. recruitment rates, treatment adherence etc.

The primary aim of this study is therefore to examine whether it is possible to conduct an RCT with this population (mothers of new-born infants) and intervention (sling use, training and support). This study has a particular focus around the feasibility of recruitment of this population and also around treatment fidelity, including whether control group participants independently engage in sling use during the trial.

While this study is underpowered to draw definitive conclusions around treatment effectiveness, it is predicted that sling use will lead to lower Postnatal Depression scores (as measured by the Edinburgh Postnatal Depression Scale (Cox, Holden, & Sagovsky, 1987), and higher wellbeing scores (as measured by the Warwick Edinburgh Mental Wellbeing Scale (WEMWBS); Tennant et al., 2007), parenting self-efficacy and responsiveness (as measured by the Parenting Sense of Competency Scale (PSCS); Gibaud-Wallston & Wandersman, 1978; and Caregiving Experiences Questionnaire (CEQ); Brennan, George & Solomon, 2013), and breastfeeding frequency and duration, in the intervention group, compared to the control group. It is predicted that any improvement seen in the scores on these measures post-intervention, in comparison to pre-intervention scores, will be significantly greater for intervention group participants, than any improvement seen for control group participants.

A secondary hypothesis is that maternal attachment style (as measured by the Experiences in Close Relationships Scale-Short (ECR-S; Wei, Russell, Mallinckrodt & Vogel, 2007) might act as a moderator of the relationship between sling use and the scores on these various measures.

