### *Sample Size*

With regards to sample size, as this is a feasibility study and hypothesis testing is not the primary aim, a normal power calculation need not be undertaken (Eldridge et al., 2016; Williams, 2016). Instead the sample size should be selected based on whether it can adequately estimate parameters that will support the design of future RCTs, e.g. recruitment rates, treatment adherence, completion rates of outcome measures etc. Furthermore it is common for the sample size of a feasibility study to be influenced by practical considerations, such as demands on time and resources (Eldridge et al., 2016).

With these considerations in mind, and following the recommendations of the National Institute of Health Research (NIHR: Research Designs Service; Hooper, 2014), it was estimated that a sample size of 50-60 participants (25-30 per condition) is likely to be both feasible and able to accurately estimate parameters for future RCTs, such as drop-out rates and standard deviations which could be used to determine future sample sizes.

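### The pre-intervention score is planned as a repeated outcome rather than a covariate: the resulting group-by-time contrast is valid but less precise than a baseline-adjusted difference

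*Protocol*

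**What the plan says.** The protocol's Proposed Analysis names the model: "A mixed ANCOVA will be used to evaluate the relationship between sling provision and maternal mental health, wellbeing and parenting". It names the comparisons: "This will include a comparison of both within-group pre- and post-intervention scores, and a between-group comparison of intervention vs. control group scores". It also names the covariates: "Attachment will be included as two covariates, as the measure of attachment used in this study produces two scores". No section makes the T1 value of an outcome a covariate.

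Aims and Hypotheses gives the prediction that this model would test: "any improvement seen in the scores on these measures post-intervention, in comparison to pre-intervention scores, will be significantly greater for intervention group participants", with controls as the comparator.

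Under Data Collection, T1 is completed before the intervention group's sling session. Most scales are taken at T1 and T3; the EPDS is also taken at T2.

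The Sample Size section says that "a normal power calculation need not be undertaken" and sets the size on practical grounds: "it was estimated that a sample size of 50-60 participants (25-30 per condition) is likely to be both feasible". Among the study's products it lists "standard deviations which could be used to determine future sample sizes".

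**The concern.** In a mixed model with time as the within-subject factor, the T1 score is one of the outcomes. The term that answers the stated hypothesis is then group by time, which for two time points is the difference between arms in mean change. Subtracting the whole baseline score, instead of regressing on it, adds noise unless the pre-post correlation is very high. With 25 to 30 women per arm, precision is scarce, and the T1 scores needed to recover it are already collected.

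There is also a question of which term will be reported. The Proposed Analysis mentions a between-group comparison of scores without saying at which time. The standard output of a mixed ANCOVA includes a group main effect that averages over all time points. Because T1 precedes the sling session, including it in that average pulls the estimate towards zero.

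**Working it through.** **Inputs.** From the protocol: 1:1 allocation, 25-30 per arm, T1 before the intervention, attachment scores as the only covariates. Not in the protocol, so assumed: a common SD *s* at each time point and a correlation ρ between time points of 0.3 to 0.8. There is no stated power, effect size or SD, so no figure of the plan's own can be reproduced.

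**Step 1. Precision of the two contrasts.** Per-woman variance:

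- Group by time (change score): 2(1 − ρ)s²
- Adjusted for T1: (1 − ρ²)s²
- Ratio, planned to adjusted: 2(1 − ρ)/(1 − ρ²) = 2/(1 + ρ)

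The standard error of the difference between arms is the square root of (variance × 2/n). In SD units with n = 30 per arm:

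| ρ | Planned variance | Adjusted variance | Ratio | SE planned | SE adjusted | 30 per arm as planned equals, if adjusted |
|---|---|---|---|---|---|---|
| 0.3 | 1.40 | 0.91 | 1.54 | 0.306 | 0.246 | 19.5 per arm |
| 0.5 | 1.00 | 0.75 | 1.33 | 0.258 | 0.224 | 22.5 per arm |
| 0.7 | 0.60 | 0.51 | 1.18 | 0.200 | 0.184 | 25.5 per arm |
| 0.8 | 0.40 | 0.36 | 1.11 | 0.163 | 0.155 | 27.0 per arm |

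The last column is 30(1 + ρ)/2. For ρ below 0.5 the planned variance exceeds s², so the change score is then less precise than the T3 score alone.

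**Step 2. What the time-averaged group main effect would estimate.** Let the true effect be *d* after the intervention and zero at T1.

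- Scales at T1 and T3: (0 + d)/2 = d/2
- EPDS at T1, T2 and T3, with the full effect at T2 and T3: (0 + d + d)/3 = 2d/3

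Its information about *d*, relative to the T1-adjusted T3 difference, is:

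- Two time points: (1 − ρ)/2, which is 35%, 25% and 15% at ρ = 0.3, 0.5 and 0.7
- EPDS: 4(1 − ρ²)/[3(1 + 2ρ)], which is 76%, 50% and 28% at the same values

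**Step 3. Check by simulation.** Two time points, n = 30 per arm, d = 0.5 SD (assumed), ρ = 0.5, two attachment covariates unrelated to the outcome, 4,000 trials:

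| Term | Mean estimate | SD of estimate | Power |
|---|---|---|---|
| Group by time | 0.501 | 0.261 | 46% |
| Group main effect | 0.245 | 0.225 | 18% |
| Adjusted for T1 | 0.499 | 0.231 | 57% |

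Group by time and the adjusted difference both recover 0.5; the main effect recovers about half. The simulated variance ratio is 0.261²/0.231² = 1.28, slightly below the 1.33 of the formula, because estimating one more coefficient costs a little at this sample size.

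**The case against.** The strongest reply is that nothing here is an error. The tested prediction is that improvement "will be significantly greater for intervention group participants, than any improvement seen for control group participants". That is the group-by-time term, which is unbiased and not diluted. It also sets the within-group change against the change in controls, so the plan does not rely on uncontrolled pre-post change. All of this stands.

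A reader might infer that the plan halves the treatment effect. The protocol does not support that. It never names the time-averaged main effect as the effect estimate, and the halving applies only to scales with two time points, not to the EPDS, its primary depression measure.

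A reader might also infer that the plan delivers the wrong SD for sizing the next trial. That does not follow either. The Sample Size section does not say that its SDs come from the mixed model's error term, and it does not say how a future trial would be analysed. Raw SDs and the T1-T3 correlation can be computed whatever model is fitted.

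The consequence is limited. The protocol calls the study underpowered and its outcome comparisons preliminary, and no stated figure changes. If ρ is high the loss is small.

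The model is not written out, and detail of that kind may sit in a statistical analysis plan that is not shown. However, the protocol does fix the model, the comparisons and the covariate list, and T1 is not on that list. The precision point rests on that.

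**Conclusion.** The concern holds as a point about efficiency and clarity, not validity. The planned group-by-time contrast has 54%, 33%, 18% or 11% more variance than a T1-adjusted comparison at ρ = 0.3, 0.5, 0.7 or 0.8. These figures assume equal SDs at T1 and T3, and the protocol gives no value of ρ. The gain from adjusting is essentially free.

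The dilution is conditional. It arises only if the between-group comparison is taken from the main effect over all time points, giving d/2 for scales at T1 and T3. The 2d/3 figure for the EPDS also assumes the full effect at T2 and T3. The wording leaves that possibility open and should close it.

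One limit applies to either analysis. Women are randomised in pregnancy, without blinding, and complete T1 after the birth, so knowledge of allocation could affect T1.

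**What to change.** In Proposed Analysis, replace the sentence on comparisons with wording to this effect:

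*For each continuous scale, the treatment effect is the difference between arms at T3 (for the EPDS, also at T2), from a model with the T1 score of that scale and the two attachment scores as covariates, reported with a 95% confidence interval.*

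Then add that:

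- neither the group main effect averaged over time nor the within-group pre-post change is interpreted as the treatment effect;
- the raw SD, the residual SD and the T1-T3 correlation are reported for each scale as inputs for sizing a future trial;
- T1 is collected after unblinded randomisation, so T1 scores are compared between arms descriptively;
- the feeding item (formula, breast or both) is categorical and has its own analysis.

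The cost is a change of wording and one extra coefficient per model. Data Collection already schedules these scales at T1.
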